### Allocation and randomization

Participants will be randomly assigned to one of the two intervention groups, namely, the reflex locomotion group or the Bobath therapy group.

Concealed allocation will be performed with a computer-generated random table of numbers created by an external statistician who will not be involved in the analysis or interpretation of the results. Individual, sequentially numbered tokens will be prepared for the random assignment. The cards will be placed in sealed, opaque envelopes, which will be opened by an external evaluator. The assignment to treatment will be revealed to the participants after the initial results are collected.

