**Methods and analysis:**

This is a randomized controlled trial on the effectiveness of two neurorehabilitation techniques in patients with multiple sclerosis conducted at the University of Salamanca. The research will take place at the Faculty of Nursing and Physiotherapy, University of Salamanca. The study will be conducted from June 2023 to June 2024. The reflex locomotion group will receive individual sessions of therapy (*n* = 27), and the Bobath concept group (*n* = 27) will receive the same number of sessions. Both groups will receive two sessions per week for 12 months. The measurement variables will be the Berg Balance Scale, the Tardieu Scale, the Cognitfit Program, Maximum Inspiratory Pressure, and Lacrimal Biomarkers.

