### Participants: inclusion/exclusion criteria

A total of 50 participants will be recruited from the general population with a diagnosis of multiple sclerosis according to the Expanded Disability Status Scale who attend their neurology consultation at the University Hospital of Salamanca. The participants in this study will be adults, aged between 20 and 60 years, of both sexes. All subjects will sign a written informed consent form before any data are collected.

Exclusion criteria will be as follows: (1) Participants with multiple sclerosis with an EDSS scale score equal to or higher than 7.0 will be excluded, (2) Pregnant women, (3) Oncology patients, (4) Non-acceptance and non-signing of the informed consent, (5) Refusal to participate in the study, (6) Patients with severe cognitive impairment that does not allow them to understand the development of the study, (7) Patients with cardiovascular instability, (8) Patients who do not complete at least 75% of the scheduled sessions, (9) Patients who do not present any of the contraindications contemplated for reflex locomotion.

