### Power and sample size

The sample size was calculated using the G^*^power Software (version 3.1.7), resulting in a minimum of 54 participants for the development of the study. The estimated effect size for the main outcome measures established in this study was 0.25. A power of the statistical test of 0.95, an alpha error of 0.05, a correlation between repeated measurements of 0.5 (two groups, two measurements), a sphericity correction coefficient of 1, and a loss percentage of 20% are taken into account.

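### No restriction or stratification is stated for allocation, and the model leaves out EDSS: the test stays valid, but precision is lost as far as disability predicts change

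*Protocol article*

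**What the plan says.** The section Allocation and randomization gives one method of generating the sequence, a "computer-generated random table of numbers created by an external statistician". It then describes the implementation: "Individual, sequentially numbered tokens will be prepared for the random assignment", held in sealed opaque envelopes that an external evaluator opens. It states no allocation ratio, block size, stratification factor or minimisation. It does not call the scheme simple or unrestricted either.

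The abstract gives 27 patients to each arm; for the second arm it says "the Bobath concept group (*n* = 27) will receive the same number of sessions". Power and sample size agrees on the total, "resulting in a minimum of 54 participants for the development of the study", while the Participants section and Risk factor 1 under Limitations both give 50.

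On disability, the Participants section sets only an upper limit: patients with an "EDSS scale score equal to or higher than 7.0 will be excluded". The Tailoring paragraphs for both interventions describe the subjects as widely heterogeneous. Statistical methods fixes a repeated-measures ANOVA with time (before and after treatment) within subjects and treatment group between subjects. It names no covariate.

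**The concern.** Nothing in the described procedure produces equal arms or balances disability, and nothing in the described model takes disability into account. With about 27 patients per arm and EDSS running up to just under 7.0, chance differences in disability between the arms are to be expected.

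Disability could bear on how much a patient can change. The Berg scale, for example, stops at 56, so a mildly disabled patient has little room to gain. If EDSS predicts change, leaving it out of both the allocation and the model leaves explainable variation in the error term. The one result the trial obtains may then be hard to separate from case mix when it is read. Two active techniques are being compared, so a modest loss of precision is worth avoiding if it costs little.

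**Working it through.** **Inputs.** From the article: total 54 and 27 per arm; effect size 0.25 (read as Cohen's f, since the scale is not named); power 0.95; alpha 0.05; correlation 0.5; two groups; two measurements; sphericity coefficient 1. Assumed, because the article gives no EDSS distribution: prevalence of the higher EDSS level 20%, 30% or 50%; correlation of baseline EDSS with change 0.3 or 0.5.

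**1. The plan's own figure.** For the time-by-group interaction, λ = f² × N × m / (1 − ρ) = 0.0625 × 54 × 2 / 0.5 = 13.5, with 1 and 52 degrees of freedom. Power is 0.9501, and N = 52 gives 0.942, so 54 is reproduced. It is reached before any allowance for the stated 20% loss, which is a separate matter.

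**2. Arm sizes if the table is unrestricted.** With one arm ~ Binomial(54, 0.5):
- P(exactly 27/27) = 0.108.
- P(23/31 or worse) = 0.341; P(22/32 or worse) = 0.220.
- The central 95% range for one arm is 20 to 34.

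The power cost follows from multiplying λ by 4·n₁·n₂/N². At 23/31 this factor is 4 × 23 × 31 / 54² = 0.978 and power is 0.946. At 20/34 it is 0.933 and power is 0.936. Averaged over all splits, power is 0.946, a loss of 0.4 points. Unequal arm size is therefore a minor issue.

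**3. Balance on a two-level EDSS factor.** Probability that the arms differ by 20 percentage points or more:

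| Assumed prevalence (patients of 54) | Unrestricted | Fixed 27/27, no strata |
|---|---|---|
| 20% (11) | 8% | 4% |
| 30% (16) | 12% | 13% |
| 50% (27) | 14% | 10% |

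The first column is from 200,000 simulated lists, the second from the exact hypergeometric distribution. The second column is not monotone because only certain gaps are possible with 27 per arm. For EDSS as a continuous score at 27/27, the standardised baseline difference has SD √(1/27 + 1/27) = 0.272. It exceeds 0.25 in absolute value in 36% of trials and 0.5 in 7%.

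**4. Effect on the test.** With two time points, the time-by-group test is a comparison of change scores, so a stable difference in level between the arms cancels. Only an effect of EDSS on change remains. Simulating simple randomisation of 54 with a covariate correlated 0.3 or 0.5 with change and no treatment effect, the unadjusted test rejected in 5.1% and 5.0% of 40,000 trials. Type I error is intact.

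**5. Precision recovered by the model.** Adjusting for a baseline covariate that correlates r with change divides the error variance by 1/(1 − r²) and costs one degree of freedom (52 to 51):
- r = 0: λ = 13.5, power 0.950.
- r = 0.3: λ = 13.5 / 0.91 = 14.8, power 0.965.
- r = 0.5: λ = 13.5 / 0.75 = 18.0, power 0.986.

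**6. What stratified blocks deliver.** With two equal EDSS strata (assumed) and 54 patients, from 20,000 simulated lists per block size:

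| Block size | Largest possible arm difference | Exactly 27/27 | Power at worst split |
|---|---|---|---|
| 2 | 2 | 75% | 0.950 |
| 4 | 4 | 59% | 0.949 |
| 6 | 6 | 55% | 0.948 |

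Within each stratum the difference is at most half a block.

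**The case against.** The strongest objection is that the article does not say the table is unrestricted. A computer-generated table can order a fixed deck of 27 + 27 cards or produce blocks, the abstract's equal arms fit such a scheme, and an article may leave block and stratum details to the full protocol. This stands. A reader might infer plain simple randomisation, but the text does not establish it, so the figures in step 2 are conditional. The balance figures for a fixed 27/27 split do not depend on that inference, and the model without a covariate is stated outright.

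Second, a reader might infer that disability imbalance would bias the comparison, so that an apparent difference is merely case mix. The documents do not support that. The planned test compares change, which removes stable level differences, and its type I error already allows for chance imbalance. What remains is lost precision, and only as far as EDSS predicts change.

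Third, a reader might expect stratified blocks to secure 27 per arm. They bound the difference but give exactly 27/27 in only 55% to 75% of lists. Nor does any scheme fix the numbers analysed: the Participants section excludes patients attending fewer than 75% of sessions, Risk factor 2 allows a new subject after an MS attack, and the target itself is 50 or 54.

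Fourth, Risk factor 1 restricts selection to relapsing-remitting disease and to patients expected to benefit, which may narrow the EDSS range by an unknown amount. This is fair; it would shrink the gain and leaves the direction unchanged.

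**Conclusion.** The point holds as a low-cost improvement and identifies no error in the design. As described, neither allocation nor analysis uses EDSS, although the sample is small and heterogeneous. If the table is unrestricted, 27/27 arises in 11% of lists, at negligible cost in power. Without stratification, a 20-point gap in a two-level EDSS factor occurs in about 4% to 13% of trials at a fixed 27/27 and 8% to 14% under simple randomisation, so most trials would show no such gap. The test is valid in every case.

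The quantifiable gain comes from the model: power at 54 goes from 0.950 to about 0.965 or 0.986 if EDSS correlates 0.3 or 0.5 with change, and there is practically no gain if it does not predict change. These sizes rest on the assumed prevalences and correlations, on reading 0.25 as Cohen's f, and on 54 patients analysed.

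**What to change.** First, state in the allocation section which restriction is used, if the full protocol already specifies one. If none is specified, have the external statistician generate permuted blocks of randomly varying size, stratified by two EDSS levels with a cut-point fixed in advance, and keep the block sizes concealed. This closely bounds the arm difference and should not be presented as guaranteeing 27/27.

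Second, whatever the allocation method, add baseline EDSS and its interaction with time to the repeated-measures model. The interaction is the term that matters, because the treatment test concerns change.

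The cost is one revised list, two envelope sets and one degree of freedom. EDSS is already needed for eligibility, so no extra patients or staff are required. The real downside is some predictability: the trial has a single site and an unblinded clinician, so very small fixed blocks should be avoided.

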## Methods and analysis

### Study design and setting

A double-blind randomized controlled trial will be conducted at the Faculty of Nursing and Physiotherapy, University of Salamanca (Spain), according to the consolidated standards of reporting trials (CONSORT) statement (25). The current treatment protocol is described according to the recommendations of SPIRIT (26).

The protocol of this trial received the approval from the Ethics Committee of the University of Salamanca (record number 896) and will be conducted according to the Declaration of Helsinki. The clinical trial was registered at ClinicalTrials.gov (registration number NCT05558683).

The study will be conducted between 1 July 2023 and 1 June 2024 in the Faculty of Nursing and Physiotherapy at the University of Salamanca.

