### Blinding

Participants will be blinded to their group assignment. Because of the nature of the intervention, the clinician cannot be blinded. In addition, the statistical analysis will be performed by an independent statistician who will be unaware of the intervention group. The person in charge of data collection will also be blinded.

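### The trial is called double-blind and its participants blinded, yet participants are to be told their assignment after the initial assessment

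*Protocol article*

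**What the plan says.** Three sections of the protocol article bear on who is blinded.

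- **Study design and setting:** "A double-blind randomized controlled trial will be conducted". The label is used only here; the Abstract describes a randomized controlled trial without it.
- **Allocation and randomization:** "The assignment to treatment will be revealed to the participants after the initial results are collected". The same section describes concealment: "The cards will be placed in sealed, opaque envelopes, which will be opened by an external evaluator".
- **Blinding:** "Participants will be blinded to their group assignment". On the therapist: "Because of the nature of the intervention, the clinician cannot be blinded". On measurement: "The person in charge of data collection will also be blinded". The section adds that the analysis will be done by a statistician who does not know the group.

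The Outcomes section places a baseline assessment first, then outcome measurements at 3, 6 and 12 months, coded by someone outside the intervention. The five primary domains are respiratory function (maximum inspiratory pressure), balance (Berg), spasticity (Tardieu), reaction time (CogniFit) and tear lipids.

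**The concern.** A participant who has been told the assignment is not blinded to it, so the Allocation and Blinding sections cannot both be right. The therapist is openly unblinded. If participants are unblinded too, neither of the two parties present at every treatment session is blind, and the double-blind label describes a property the design does not have.

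At stake is the risk of bias the trial can claim. Maximum inspiratory pressure requires a forced inspiration and reaction time requires the participant's own response, so both can be influenced by what the participant knows or expects. Blinding the person who records the result does not remove that route. A reader who relied on the label would rate performance bias lower than the described procedures allow.

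**Working it through.** The document gives no figure on this point, so the check compares its statements.

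**Step 1. Who is said to be blinded, and what the procedures support**

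| Party | Statement on blinding | Procedure described | Supported as written? |
|---|---|---|---|
| Participant | Blinded (Blinding section) | Told the assignment after the initial results (Allocation and randomization) | No |
| Treating clinician | Not blinded, with the reason given (Blinding section) | Delivers the therapy | Not blinded, and disclosed |
| Data collector | Blinded (Blinding section) | Outcomes coded by someone outside the intervention (Outcomes) | Yes |
| Statistician | Unaware of group (Blinding section) | Nothing contrary | Yes |

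**Step 2. Does any reading of the initial results rescue participant blinding?**

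- *Baseline assessment.* This is the natural reading, because the Outcomes section puts baseline first. Participants then know their arm at all three outcome visits (3, 6 and 12 months).
- *First follow-up at 3 months.* Participants then know their arm at two of the three outcome visits (6 and 12 months), including the one that closes the 12-month treatment period.
- *Final assessment.* Only this reading would keep participants blind throughout, and the word initial cannot bear it.

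No tenable reading leaves participants blind through the 12-month outcomes.

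**Step 3. Which primary outcomes are exposed to participant knowledge?**

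- *Maximum inspiratory pressure and reaction time:* directly exposed, because the result depends on the participant's effort or response.
- *Berg and Tardieu:* scored by a rater, and so protected on the rater's side as long as the data collector stays blinded as stated.
- *Tear lipids:* a laboratory assay which, according to the Highlights, is run by personnel outside the study team. It is the least exposed.

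**The case against.** The strongest counter-arguments deserve weight.

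- **The unblinded therapist is disclosed.** A double-blind label meaning participant and assessor is compatible with an unblinded provider. This stands: the therapist's status alone contradicts nothing. The label fails because the participant limb fails.
- **The envelope opener.** A reader might infer that the external evaluator who opens the envelopes also assesses outcomes, so that assessor blinding is lost as well. The documents do not support this. Nothing says the two are the same person, the Blinding section says the data collector is blinded, and the Outcomes section has coding done by someone outside the intervention. What remains is an ambiguous job title that one sentence would settle.
- **Only one safeguard left.** A reader might also conclude that data-collector blinding is all that remains. It is not, because the statistician is blinded too.
- **Direction and size of bias.** The Hypotheses section favours reflex locomotion, so it is tempting to say expectation will favour that arm, or to attach a fraction of a standard deviation to it. The document does not say participants are told the hypothesis. Both arms are active, individual physiotherapy with the same number and length of sessions in the same place. No figure for an expectation effect is given, and any number would be an outside assumption.
- **Which sentence is the error?** The text does not show whether the disclosure sentence or the participant-blinding sentence is the mistake. This stands, and it is why the request is to reconcile the sections first.

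None of these removes the conflict between the two sections on participants.

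**Conclusion.** The point holds as a direct contradiction about participant blinding, with high confidence. A stated design property is wrong as written: participants are declared blinded in one section and informed in another, at the latest before the 6- and 12-month visits. With the therapist's disclosed status, the procedures support blinding of the data collector and the statistician and of no one else. The consequence is greatest for maximum inspiratory pressure and reaction time. The document allows neither the size nor the direction of a bias to be derived, so none is claimed. The conclusion assumes that the disclosure sentence means what it says and that the data collector and statistician remain blinded as stated. It does not extend to a breach of assessor blinding or of allocation concealment.

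**What to change.** 1. Reconcile the Study design and setting, Allocation and randomization, and Blinding sections so that they say the same thing about who is blinded and until when.
2. If disclosure after baseline stands, remove the double-blind label and the participant-blinding sentence. Replace them with: *outcome-assessor- and analyst-blinded; participants and therapists not blinded*. Report the trial in those terms.
3. As a minor clarification, state that the external person who opens the envelopes has no role in outcome assessment. Leave the task with an external person; moving it to the treating therapist could weaken allocation concealment.

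Asking participants not to mention their therapy at assessments, or recording the assessor's guess of the arm, would be optional additions and corrects no error in the text.

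The cost is a few sentences and a less favourable blinding label. If disclosure stands, nothing changes in sample size, visits, treatment or analysis.

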### Blinding

Participants will be blinded to their group assignment. Because of the nature of the intervention, the clinician cannot be blinded. In addition, the statistical analysis will be performed by an independent statistician who will be unaware of the intervention group. The person in charge of data collection will also be blinded.

### Statistical methods

Statistical analysis will be performed using the SPSS 27.0 statistical software for Windows (SPSS Inc., Chicago, IL; version 27.0). The normality of the sample will be checked using the Shapiro-Wilk test, and if it follows a normal distribution, an analysis of variance (ANOVA) of repeated measures *p* will be used, with time (pre-treatment and post-treatment) as an intra-group factor and Vojta and Bobath groups as the inter-group factor, all with a Bonferroni correction. Statistical analysis will be performed with a confidence level of 95%, so a *p*-value of < 0.05 will be considered significant values.

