### Outcomes

In the baseline assessment, all variables, including sociodemographic variables, will be measured. Subsequently, all outcome variables will be measured at 3, 6, and 12 months and coded by a person external to the intervention.

Personal and sociodemographic variables are as follows:

Age (years).Sex (male or female).Weight (kg), height (m), body mass index (BMI; kg/m^2^).Study level (no studies, basic education, secondary school, or superior studies).Marital status (single, married, separated, divorced, or widowed).Time since diagnosis of MS (years and months).Smoking (yes or no).Pharmacological treatment (name and number of pills per day).Comorbidities (name).

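### The pre/post ANOVA is valid but leaves the 3- and 6-month visits unused and gives up about 25% of precision (at the plan's correlation of 0.5) by not adjusting for baseline

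*Protocol article*

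**What the plan says.** The Outcomes section of the protocol article sets four measurement occasions. On baseline it says "In the baseline assessment, all variables, including sociodemographic variables, will be measured"; after that, "all outcome variables will be measured at 3, 6, and 12 months".

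Statistical methods fixes the analysis as a repeated-measures ANOVA "with time (pre-treatment and post-treatment) as an intra-group factor and Vojta and Bobath groups as the inter-group factor". The time factor therefore has two levels. Baseline enters only as one of them, and no covariate is named.

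Power and sample size uses the same two-occasion structure. It states "The estimated effect size for the main outcome measures established in this study was 0.25" and "A power of the statistical test of 0.95, an alpha error of 0.05", with two groups, two measurements, a correlation of 0.5 between measurements, a sphericity coefficient of 1 and 20% loss. The result is 54 participants. The Participants section and the first limitation each give 50.

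**The concern.** The schedule has four occasions and the analysis has two. Two consequences follow from the text as written.

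- The 3- and 6-month values of every outcome have no role in the stated test.
- With only two levels, the group-by-time interaction is a t test on change from baseline. In a randomised trial, adjusting the final value for baseline estimates the same between-arm difference with smaller variance whenever the correlation is below 1. The information needed is already scheduled for collection.

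What is at stake is efficiency. In a trial of about 50 participants with 20% loss expected, the choice between these two analyses can move power by several percentage points at no recruitment cost.

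**Working it through.** **Inputs.** From Power and sample size: f = 0.25, α = 0.05, target power 0.95, ρ = 0.5, 2 groups, 2 measurements, ε = 1, 20% loss, N = 54. From Participants and Limitations: 50 recruited. σ is the SD of a single measurement, taken as equal at both occasions.

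**1. Reproduce the plan's figure.** For the within-between interaction, λ = f²·N·m/(1 − ρ) = 0.0625 × 54 × 2/0.5 = 13.5, with 1 and 52 degrees of freedom. Power is 0.9501; N = 52 gives 0.9424. So 54 is reproduced as the two-measurement interaction. The between-groups main-effect version would need 158. The intermediate visits therefore enter neither the sizing nor the stated test.

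**2. Express the effect as a difference.** In a 2 × 2 interaction, f = 0.25 moves each cell by ±0.25σ, so the between-arm difference in change is 4 × 0.25σ = 1.0σ. Check: the change-score variance is 2(1 − ρ)σ² = 1.00σ², and the t test has λ = (N/4) × 1.0²/1.00 = 54/4 = 13.5, as in step 1.

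**3. Compare variance with and without baseline adjustment.** The change score has variance 2(1 − ρ). The baseline-adjusted value has variance 1 − ρ². The ratio is (1 + ρ)/2, so the precision lost is (1 − ρ)/2.

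| ρ | Change score | Adjusted | Precision lost | SE reduction from adjusting |
|---|---|---|---|---|
| 0.3 | 1.40 | 0.91 | 35% | 19.4% |
| 0.5 | 1.00 | 0.75 | 25% | 13.4% |
| 0.7 | 0.60 | 0.51 | 15% | 7.8% |
| 0.8 | 0.40 | 0.36 | 10% | 5.1% |

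**4. Power for a 1.0σ difference at ρ = 0.5.** The change score has λ = (N/4)/1.00 on N − 2 df. The adjusted analysis has λ = (N/4)/0.75 on N − 3 df.

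| Analysed | Origin | Change score | Adjusted |
|---|---|---|---|
| 40 | 0.8 × 50 | 0.869 | 0.945 |
| 43 | 0.8 × 54 = 43.2 | 0.893 | 0.959 |
| 54 | no loss | 0.950 | 0.986 |

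About 42 analysed participants reach 0.95 with adjustment (power 0.954), against 54 without.

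**5. The same comparison at other correlations, 40 analysed.** Power is 0.740 against 0.898 at ρ = 0.3, 0.978 against 0.991 at 0.7, and 0.998 against 0.999 at 0.8.

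**6. What the intermediate visits add.** Assume equal correlation 0.5 between all visits, 27 per arm, and 20% missing at 12 months only, so 21.6 complete and 5.4 partial per arm. The variances of the 12-month contrast, in units of σ², are:

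- change score, complete pairs: 2 × 1.00/21.6 = 0.0926
- baseline-adjusted, complete pairs: 2 × 0.75/21.6 = 0.0694
- longitudinal model, all visits: baseline, 3 and 6 months together explain 0.375 of the 12-month variance, baseline alone 0.25. This gives 2 × (0.625/21.6 + 0.125/27) = 0.0671

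The visits cut the variance by a further 3% (0.0671/0.0694 = 0.967). The total loss of the change-score test against the longitudinal model is 1 − 0.0671/0.0926 = 27.5%. With no missing data under this correlation pattern, the visits add nothing to the 12-month contrast.

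**The case against.** The strongest reply is that the planned test is sound. Under randomisation the change-score comparison is unbiased with complete data, and sizing and analysis agree exactly, so the plan never relied on the extra precision. That stands. The point is an available improvement, not an invalid test.

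It is also fair that the gain depends on a planning correlation. If the true value is near 0.8, both analyses have power above 0.99 for a 1.0σ difference and the change hardly matters.

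A reader might infer more than the document supports:

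- **That the 25% comes from discarding visits or incomplete participants.** It comes from baseline adjustment alone; the intermediate visits contribute about 3% more under the assumptions in the working.
- **That the deciding effect is unidentified.** The Hypotheses section claims a greater improvement with one therapy than with the other, and 54 is reproduced as the interaction, not as the group main effect. Together these point to the group-by-time test.
- **That the plan adopts a biased completer analysis.** A two-level ANOVA needs both values, but the article states no rule for missing visits. An article commonly leaves that to the full plan.
- **That the normality condition is itself a defect.** The ANOVA is conditional ("and if it follows a normal distribution, an analysis of variance (ANOVA) of repeated measures") and no fallback is named, but that fallback is also detail for the full plan. The article gives no Tardieu scoring and no lipid distribution on which to prescribe outcome-specific methods.

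**Conclusion.** The concern holds as an efficiency point and as an unreconciled difference between the four-visit schedule and the two-level analysis. At the plan's ρ = 0.5 the stated test gives up 25% of the attainable precision, about 13% in standard error. With 40 to 43 analysed, baseline adjustment brings power from 0.87–0.89 to 0.945–0.96, at or close to the stated 0.95. The range is 35% of precision at ρ = 0.3 down to 10% at 0.8, where the power gain is negligible.

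These figures assume equal variance at both occasions, a linear relation between baseline and follow-up, and a 1.0σ difference held fixed as ρ varies. The 3% for the intermediate visits also assumes equal correlation between visits and loss at 12 months only.

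Whether 54 allows for the 20% loss is a separate question and does not raise the weight of this one. Should-fix; a free improvement.

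**What to change.** Reconcile Outcomes, Power and sample size, and Statistical methods so that all three describe the same occasions and the same test.

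Replace the pre/post ANOVA with a longitudinal mixed model for each outcome:

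- **Response:** the 3-, 6- and 12-month values.
- **Fixed effects:** baseline value of the outcome, group, visit and group-by-visit.
- **Population:** all randomised participants with any follow-up value.
- **Deciding test:** the between-arm difference at 12 months. Differences at 3 and 6 months describe the time course.

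The sample-size paragraph should then name this test. The existing 54 is conservative for it at ρ = 0.5, where about 42 analysed participants suffice for 0.95 power.

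The cost is a change of wording before unblinding and somewhat more modelling work. No visit, measurement or participant is added.
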